### Active cohort

The active cohort will measure malaria infection, anaemia, and malnutrition incidence in the intervention and control study populations in Cameroon and Côte d’Ivoire. The sampling frame for the active cohort will consist of the children whose primary caregiver provided consent for participation in the passive cohort (Table 1). Children between 6 and 9 months and 10 weeks and 6 months of age at recruitment in Cameroon and Côte d’Ivoire, respectively, will be approached for inclusion. Targeting these age ranges will maximize study power to measure differences between the PMC intervention and standard of care in each country within the 18-month study period. The target age range was also defined to ensure at least one sampling time point after the final potential PMC dose to observe any change in risk of malaria infection after aging out of the intervention [13]. Recruitment into the active cohort will continue until the target sample size is achieved.

At the initial household visit for children enrolled in the active cohort, field workers will record the household and child ID number assigned during the census and collect detailed information related to malaria risk factors including household construction and use of vector control interventions. A detailed questionnaire on recent fevers, malaria history, care seeking behaviours, EPI vaccines received to date, and other relevant factors will also be collected. Children will be assessed for fever, anaemia, malaria, and malnutrition. First, forehead temperature will be taken using an infrared thermometer with fever defined as those with temperature > 37.5 °C. A capillary blood sample by heel or fingerpick will be collected using a sterile lancet and aseptic technique on all children. The blood sample will be used to measure: (i) haemoglobin (Hb) levels with a photometer (HemoCue^®^ Hb 301, Angleholm, Sweden), devices, (ii) conduct a malaria rapid diagnostic test (RDT), (iii) prepare a thin and thick blood slide for malaria microscopy and (iv) to collect blood spots on filter paper. The mid-upper-arm circumference will be collected from all enrolled children to screen for malnutrition and monitor growth trajectories over time. Treatment for malaria, anaemia and malnutrition will be offered according to national guidelines. Any children with a fever or who are severely ill will be referred to the nearest health facility for treatment.

Each child in the active cohort will be followed-up for a maximum of seven visits at three-monthly intervals over 18 months, including the initial recruitment visit plus six subsequent follow-up visits (Fig. 4). During follow up visits at the household, verbal consent from the primary caregiver for continued participation of their child in the study will be recorded. A short questionnaire will be completed to collect data about any malaria or anaemia diagnosis or receipt of PMC since the last study visit, at which health facility care was sought and other relevant information. A blood sample will be collected following the same procedures outlined above.

Adverse events and safety of receiving PMC will be monitored by the MoH as part of the routine programmatic implementation of this intervention. Participant safety will be monitored throughout the study period and any adverse effects related to study procedures will be investigated using standardised procedures and managed according to national guidelines.

**Fig. 4 Fig4:**
[figure not shown]
Title: Overview of impact evaluation study activities Legend: Timeline of the impact evaluation study activities including when the different study components take place and when they overlap

### Sample size

For the passive cohort, we will monitor all eligible children enrolled in the study and will therefore, will constitute a population sample. For the active cohort, the sample size was calculated to ensure 80% power at the 5% significance level, assuming an intra-cluster correlation coefficient of 0.25, and accounting for a 3:1 sampling ratio of intervention to control to ensure sufficient power to assess any variation in PMC effectiveness according to distance to the EPI facility. However, the specific sample size for the number of EPI facilities and children to include in the active cohort was calculated separately for each study site to account for the differences in PMC implementation (Fig. 1).

In Cameroon, we expect a 30% reduction in malaria incidence in intervention compared to control areas, requiring 26 intervention and 9 control EPI facilities are required. With a 20% expected loss to follow-up rate, we require 1,560 in the intervention and 540 children in the control area over the 18 months of observation in the active cohort. In Côte d’Ivoire, the standard of care currently being implemented by the NMP is no doses, so the difference between in the number of SP contacts between arms is 5. Therefore, we expect a 40% reduction in malaria incidence in intervention compared to control areas. Accordingly, 14 and 5 EPI facilities will be required in the intervention and control areas, respectively. Assuming a conservative loss to follow-up rate of 20%, we require 1,148 and 410 children in the intervention and control areas, respectively, over the 18 months of observation in the active cohort.

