**Methods:**

We will assess the impact of PMC using passive and active monitoring of a prospective observational cohort of children up to 36 months of age at recruitment in selected study sites in Cameroon and Côte d’Ivoire. The primary and secondary outcomes include malaria, anaemia and malnutrition incidence. We will also conduct a time-series analysis of passively detected malaria and anaemia cases comparing the periods before and after PMC introduction. This study is powered to detect a 30% and 40% reduction of malaria incidence compared to the standard of care in Cameroon and Côte d’Ivoire, respectively.

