### Cameroon

Soa and Mbankomo are peri-urban areas located on the north-eastern and south-western periphery of Yaoundé, respectively (Fig. 2). Both areas have an estimated population density of 1,235 people per squared km and 15% of the population is under 5 years of age. In total, there are 39 health facilities in Soa, 12 of which are public and 28 have active CHWs. Of the 39 facilities, 20 administer EPI services and are eligible for SP administration as part of the expanded PMC programme. In Mbankomo, there are 32 health facilities, of which 4 are public and 10 have active CHWs. Of the 32 facilities, 19 administer EPI services and are eligible for SP administration as part of the standard of care PMC programme. Malaria incidence in both Soa and Mbankomo was 597 cases per 1000 children under 5 in 2020 [12]. Malaria transmission is typically highest during the two rainy seasons, from March to June and from October to November.

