### Côte d’Ivoire

Séguéla and Kani are rural areas located approximately 500 km northwest of the capital city, Abidjan (Fig. 2). The estimated population density is 45.98 people per squared km (2021) and 18% of the population is under 5 years of age. In total, there are 42 health facilities in Séguéla, all of which are public and 33 of these have active CHWs. Of the 42 facilities, 41 administer EPI services and thus are eligible for SP administration as part of the expanded PMC programme. In Kani, there are 8 health facilities, all of which are public and have active CHWs. Of the 8 facilities, all administer EPI services and thus would be eligible for SP administration if any doses were given as part of a standard of care PMC programme. According to the NMP, malaria incidence in both Séguéla and Kani was 572 cases per 1000 children under 5 in 2020 with the peak typically from April to July during the rainy season.

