### Study design

All health facilities providing EPI services in selected study sites and corresponding catchment populations will be eligible for inclusion and constitute the primary sampling unit for this evaluation. Health facilities will be randomly selected for inclusion (Fig. 3). All non-EPI/PMC facilities within the selected EPI catchment areas, will be included in the passive cohort data collection, described below (Table 1). In the selected EPI facility catchment areas, several study activities will be conducted: (i) a census to enumerate all households, primary caregivers and children under 36 to characterize the population eligible to receive PMC (0–24 months) as well as when they age out of the intervention (25–36 months), (ii) a passive cohort at health facilities to monitor clinical episodes of malaria and anaemia as well as receipt of EPI vaccinations and PMC in children under 36 months, and (iii) to monitor malaria and anaemia in a subgroup of participating children in an active cohort over an 18-month period. The same procedures will be employed in both intervention and control areas in Cameroon and Côte d’Ivoire.

**Table 1 Tab1:** Eligibility criteria for each study component in the PMC impact evaluation study

	Inclusion Criteria	Exclusion Criteria
**Health Facilities**	- Located within the target study sites - Administer EPI/PMC services	- Located outside of the target study area
**Census - Household**	- Located within the catchment area of selected health facilities - Head of household provides consent	- Located outside of the selected health facility catchment area - Head of household not present or refuses participation
**Passive Cohort - Child**	- Regularly resides in households included in the census - Age 36 months or less at time of census - Primary caregiver provides informed consent	- Head of household refused participation in the census - Primary caregiver not present or refuses participation - Not expected to reside in the selected household for the study duration - Age greater than 36 months of age at recruitment visit

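### The stated ICC of 0.25 and the stated 80% power do not fit together at the article's own incidences; the sizes fit if 0.25 is a between-facility coefficient of variation

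*Protocol article*

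**What the plan says.** The Sample size section sizes the active cohort on one clustering parameter and one power: "the sample size was calculated to ensure 80% power at the 5% significance level, assuming an intra-cluster correlation coefficient of 0.25". It plans 3:1 sampling of intervention to control.

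- Cameroon: a 30% reduction, 26 intervention and 9 control facilities, 1,560 and 540 children.
- Côte d'Ivoire: a 40% reduction, 14 and 5 facilities, 1,148 and 410 children.
- Both child counts allow for 20% loss to follow-up over 18 months.

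The Study design section makes the facility and its catchment population the cluster: these "constitute the primary sampling unit for this evaluation". The abstract repeats the claim: "This study is powered to detect a 30% and 40% reduction of malaria incidence compared to the standard of care".

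The Sample size section names no control incidence and no formula. The only incidences in the article are in the site descriptions: Cameroon "was 597 cases per 1000 children under 5 in 2020" and Côte d'Ivoire "was 572 cases per 1000 children under 5 in 2020".

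**The concern.** An ICC of 0.25 between children of the same facility is very large when 60 or 82 children are taken per facility. The effective sample shrinks to a few dozen children per control arm, which is hard to square with 80% power for reductions of 30% and 40%.

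The ICC and the between-cluster coefficient of variation k are different quantities that are easily confused. With the documented incidences treated as proportions, k = 0.25 corresponds to an ICC of about 0.08-0.09, and an ICC of 0.25 to a k of about 0.41-0.43.

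This is the only power statement in the article. If the ICC is meant literally and the documented incidences apply, a null result is likelier than not even when the intervention works as assumed, and the results are meant to inform programme decisions. If k was meant, anyone who takes the ICC from this article to size a later study will be misled.

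**Working it through.** **Inputs from the article.** 1,560/26 = 540/9 = 60 children per facility in Cameroon; 1,148/14 = 410/5 = 82 in Côte d'Ivoire. After 20% loss: 48 and 65.6. Children left: 1,248 and 432 in Cameroon; 918.4 and 328 in Côte d'Ivoire. Follow-up is 1.5 years.

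**Assumptions.** Control rates of 0.597 and 0.572 per child-year, so intervention rates of 0.4179 and 0.3432. Two-sided 5% test. Power = Φ(z − 1.96).

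**1. Trying to reproduce 80% with an ICC of 0.25.** Design effect = 1 + (m − 1) × 0.25: 12.75 for m = 48 and 17.15 for m = 65.6. Effective numbers are about 98 + 34 and 54 + 19 children.

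*Rate difference, 18 months:* variance = DE × (λ0/T0 + λ1/T1), where T is child-years.
- Cameroon: 12.75 × (0.597/648 + 0.4179/1872) = 0.01459; z = 0.1791/0.1208 = 1.483; power 31.7%.
- Côte d'Ivoire: 17.15 × (0.572/492 + 0.3432/1377.6) = 0.02421; z = 0.2288/0.1556 = 1.470; power 31.2%.

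*Log rate ratio, 18 months:* variance = DE × (1/events0 + 1/events1).
- Cameroon: 12.75 × (1/386.9 + 1/782.3) = 0.04926; z = 0.3567/0.2219 = 1.607; power 36.2%.
- Côte d'Ivoire: 17.15 × (1/281.4 + 1/472.8) = 0.09721; z = 0.5108/0.3118 = 1.638; power 37.4%.

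*Annual figure treated as a proportion:* variance = DE × (p0q0/n0 + p1q1/n1).
- Cameroon, 0.597 vs 0.418: z = 1.83; power 45%.
- Côte d'Ivoire, 0.572 vs 0.343: z = 1.75; power 42%.

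*18-month cumulative risk, 1 − exp(−1.5λ):*
- Cameroon, 0.592 vs 0.466: z = 1.28; power 25%.
- Côte d'Ivoire, 0.576 vs 0.402: z = 1.32; power 26%.

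A one-year risk gives still less, about 20%, but ignores a third of the follow-up. One-sided testing reaches at most about 57%. More children per facility would not help: with unlimited cluster size the proportion version stops at 47% and 43%.

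**2. What would make 80% true with these sizes.** At the documented incidences the ICC would have to be about 0.03-0.09 (0.055 and 0.058 on the rate-difference scale).

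Alternatively, keep the ICC at 0.25 and raise the control rate. With the rate ratio fixed, z grows with the square root of the rate, and 80% needs z = 2.80.
- Rate difference: 0.597 × (2.80/1.483)² ≈ 2.13 and 0.572 × (2.80/1.470)² ≈ 2.08 per child-year, about 3.6 times the documented figures.
- Log scale: 0.597 × (2.80/1.607)² ≈ 1.8 and 0.572 × (2.80/1.638)² ≈ 1.7, about 3 times.
- Doubling the documented rates multiplies z by 1.414. On the rate-difference scale z becomes 2.10 and 2.08, and power about 55% in both countries. On the log scale it is about 62% and 64%.

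**3. Reading 0.25 as k.** Variance = [λ0/y + k²λ0²]/c0 + [λ1/y + k²λ1²]/c1, where y = 1.5m is child-years per facility and c is the number of facilities.
- Cameroon, y = 72: (0.00829 + 0.02228)/9 + (0.00580 + 0.01092)/26 = 0.00404; z = 0.1791/0.0636 = 2.82; power 80.5%.
- Côte d'Ivoire, y = 98.4: (0.00581 + 0.02045)/5 + (0.00349 + 0.00736)/14 = 0.00603; z = 0.2288/0.0776 = 2.95; power 83.8%.

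Solving for facilities gives 8.9 control and 25.7 intervention in Cameroon at the 26:9 ratio (8.8 and 26.5 at exactly 3:1; stated 9 and 26). For Côte d'Ivoire it gives 4.5 and 13.4 at 3:1 (stated 5 and 14). The excess power there comes from rounding up; 4 control facilities would give 76%.

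**The case against.** The strongest objection is that the power figures rest on inputs the Sample size section does not name. The 597 and 572 are 2020 figures for children under 5. The active cohort is younger, is tested by RDT and microscopy every three months, and counts cases found in either cohort. The article itself says that passive detection probably understates the burden. A higher control rate was therefore possible, and a rate of 2.2 per child-year at 3:1 with an ICC of 0.25 returns 8.7/26.0 and 4.7/14.0 facilities, which also round to the stated numbers. An article may also leave the formula and control rate to the full protocol.

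Much of this stands. The 25-45% is conditional, and its upper end treats a rate as a proportion although the analysis models rates. A reader might infer that k is the only reading that reproduces the sizes; the 2.2 example shows that it is not. What does not fall away is the mismatch between printed numbers. The article states no rate near 2, and doubling its incidences does not bring power to 80%. The complaint is not that a formula is missing.

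A reader might also infer that a wrong ICC would distort the final or interim analysis. The Data analysis section does not support that: it handles repeated measures on a child with random effects or estimating equations fitted to the data, and nowhere makes the planning ICC an input.

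**Conclusion.** The concern holds in conditional form. At the only incidences the article reports, an ICC of 0.25 with the stated facilities and children gives about 25-45% power, not 80%. The rate-based versions, closest to the planned analysis, give 31-37%. This assumes that those incidences are the control rates, that the test is two-sided, that 20% are lost, and that the facility is the cluster.

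Reading 0.25 as k returns the stated power and approximately the stated facility counts in both countries without tuning any input, so a mislabelled parameter is the likely explanation. It is not proven. The 80.5% and 83.8% are normal approximations; a t-based version gives about 78% and 79%.

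It would go too far to conclude that the study is underpowered. That follows only if 0.25 is truly an ICC and the control rate is near the documented figures. Nor is the abstract necessarily wrong: if k was meant, its claim stands.

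**What to change.** Re-run the calculation and state in the Sample size section the control incidence and the formula that were actually used. The authors must supply these; the 597 and 572 should not be written in unless they were the inputs. Then take whichever case applies:

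- **0.25 was k.** Relabel it as the between-facility coefficient of variation. The 80% and the abstract stay as they are.
- **0.25 is an ICC and the documented incidences apply.** Restate the power (about 25-45%) or the detectable reduction, in the Sample size section and in the abstract.
- **0.25 is an ICC and a higher control rate was assumed.** State that rate and its basis, and keep the 80% only if it supports it.

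The cost is a rewording and one recalculation, with no change in facilities or enrolment. The downside is that the stated power may become less favourable.

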### Aims and objectives

This is a multi-site study with the primary aim to evaluate the impact of routine delivery of PMC on malaria incidence during the first two years of life. In Cameroon we will compare the effect of up to eight versus the standard of care of five doses, whilst in Côte d’Ivoire we will compare the effect of five versus zero SP doses, as the standard of care. Secondary objectives include determining any differences in: (i) severe malaria, malarial deaths, anaemia, and severe anaemia; (ii) differences in all indicators by country, delivery platform and the number and timing of doses; and (iii) any dose response effect or differences according to distance to the health facilities, as a proxy for access to care.

Evaluation of malaria interventions requires knowledge of the regional epidemiology of malaria and active and passive surveillance methods have been proposed for malaria vaccine efficacy studies. Passive case detection methods are limited to those seeking health care and are likely to underestimate burden of malaria in the community but may provide information on the clinical presentation and management of malaria relevant for planning health services. In contrast, active surveillance methods can minimise the effect of health care-seeking behaviour on malaria detection and measures of effect. It also allows for understanding the age, spatial and temporal patterns of disease in community settings. To address these issues, we will employ two approaches to address the study objectives. First, we will develop a passive cohort, which will capture routinely collected health data as part of all child visits to participating health facilities in the selected study sites. Secondly, we will form and prospectively follow an active cohort of children who will be visited at their households every three months over the study period. Reported malaria and anaemia cases in children under 5 years from the 5 years prior to the start of the study will also be collected to ensure results can be interpreted within the context of the broader malaria transmission patterns at each site.

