Where there are repeated measures per child, random effects or generalising estimating equations models will be used to adjust for non-independence of the data from the same individual. Regression models will assess factors associated with incidence of malaria infection including demographic variables, malaria history, reported vector control use, socio economic position, amongst others [17]. Transmission intensity, type of PMC delivery mode, impact of the estimated protective window of SP, and other factors will be adjusted for to assess their impact on the incidence trends [18]. Subgroup analysis will constitute assessing the impact of distance to the health facility as a proxy for access to health services according to the study endpoints highlighted above. Distance will be assessed according to tertials of distance of all study participants to their nearest health facility and as a continuous variable. Alternate model forms including interaction terms as well as semiparametric approaches to account for time-varying intervention effects to account for the expected 4-week prophylactic period of SP will be tested [19]. Because of the challenges in confirming cause of death in those who die in the community and the assumption that severe malaria cases will seek care at a health facility, only the passive cohort data will be used to assess these secondary outcomes [20]. An interim analysis will be conducted after the 4th active cohort visit and the study will be reported according to the ‘Strengthening the reporting of observational studies in epidemiology’ (STROBE) guidelines [21].

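### The 3:1 ratio is said to ensure sufficient power for any variation in PMC effectiveness by distance, but the sample size has no distance term and supports only large gradients at the incidences given

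*Protocol article*

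**What the plan says.** In the protocol article, Sample size, the calculation for the active cohort is described thus: "the sample size was calculated to ensure 80% power at the 5% significance level". Clustering enters through the phrase "assuming an intra-cluster correlation coefficient of 0.25". The allocation is given as "3:1 sampling ratio of intervention to control to ensure sufficient power to assess any variation in PMC effectiveness according to distance", meaning distance from the EPI facility. The effects named there are overall ones: "In Cameroon, we expect a 30% reduction in malaria incidence in intervention compared to control areas", and a 40% reduction in Côte d'Ivoire. The resulting numbers for Cameroon are "requiring 26 intervention and 9 control EPI facilities are required" and "we require 1,560 in the intervention and 540 children in the control area over the 18 months of observation"; for Côte d'Ivoire they are 14 and 5 facilities, with 1,148 and 410 children. No distance gradient, and no power for one, is given.

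The distance question is a stated objective. Aims and objectives lists "any dose response effect or differences according to distance to the health facilities, as a proxy for access to care" among the secondary objectives. Data analysis says "Subgroup analysis will constitute assessing the impact of distance to the health facility as a proxy for access to health services", with distance taken both in tertiles and as a continuous variable.

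**The concern.** The Sample size section makes a positive power claim for the distance question and credits it to the allocation ratio. Effectiveness is a contrast between intervention and control areas. Whether it varies with distance therefore has to be judged against control children at the same distances, because incidence may change with distance without PMC. The small control arm limits that comparison, and a near-far contrast uses only part of the data that give 80% power for the overall effect.

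Distance stands in for access to care, and the results are meant to inform programme decisions. If the design is described as sufficiently powered for any variation, an inconclusive interaction carries more weight than the data can give it.

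**Working it through.** **1. The plan's own figures.** Inputs from Sample size: two-sided 5% (two-sidedness assumed), 80% power, 3:1, rate ratios 0.70 and 0.60, 20% loss, 18 months. Children per facility are 1,560/26 = 60 and 1,148/14 = 82. After loss, that gives y = 60 × 0.8 × 1.5 = 72 and 82 × 0.8 × 1.5 = 98.4 child-years per facility. The section names no control rate, so I take the 2020 under-5 incidences under Study site: 0.597 and 0.572 per child-year. The 0.25 is read as a between-facility coefficient of variation k. Read as a true intra-cluster correlation, it would need about 21 to 48 control facilities in Cameroon and 12 to 27 in Côte d'Ivoire, depending on the formula.

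Control facilities = (1.96 + 0.84)² × [(λ0/y + k²λ0²) + (λ1/y + k²λ1²)/3] / (λ0 − λ1)²

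- Cameroon (λ1 = 0.4179): 7.85 × [0.0306 + 0.0167/3] / 0.0321 = 8.84. This gives 9 control and about 26.5 intervention (26 stated); power at 26:9 is 80.5%.
- Côte d'Ivoire (λ1 = 0.3432): 7.85 × [0.0263 + 0.0109/3] / 0.0523 = 4.48. This gives 5 control and about 13.4 intervention (14 stated); power at 14:5 is 83.8%.

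The stated numbers are thus explained by the overall effect alone.

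**2. Power for the distance interaction.** Compare the far-tertile with the near-tertile rate ratio, with equal tertiles, active cohort only, each country alone and Poisson counts:

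SE² = 2/E0 + 1/E1near + 1/E1far (events per tertile); power = Φ(ln(RRfar/RRnear)/SE − 1.96)

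- Cameroon, 40% reduction near and 20% far. E0 = 540 × 0.8 × 1.5 × 0.597/3 = 129. E1 = 372.5 × 0.6 = 223.5 near and 372.5 × 0.8 = 298 far. SE = 0.153; Φ(0.288/0.153 − 1.96) = 47%.
- Côte d'Ivoire, 50% near and 30% far. E0 = 93.8; E1 = 131.3 and 183.9. SE = 0.185; Φ(0.336/0.185 − 1.96) = 44%.

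| Near-far gradient | Cameroon | Côte d'Ivoire |
|---|---|---|
| 10 points | 15% | 15% |
| 20 points | 47% | 44% |
| 30 points | 81% | 78% |
| 40 points | 97% | 96% |

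The detectable ratio of rate ratios at 80% power, with the SE taken at the average effect, is exp(2.80 × 0.152) = 1.53 and exp(2.80 × 0.184) = 1.68.

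**3. Sensitivity, 20-point gradient (Cameroon; Côte d'Ivoire).**

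- No loss: 56%; 53%.
- Continuous distance, 20% loss: 52%; 49%.
- Overdispersion 1.5: 34%; 32%.
- Distance slope varying between facilities (SD 0.25): 36%; 32%.
- Assumed rate 1.0 per child-year: 68%; 67%.
- Assumed rate 1.5 per child-year: 85%; 84%.
- Countries pooled at the documented rates: about 74%.

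**4. The ratio.**

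| Design, 20-point gradient | Cameroon | Côte d'Ivoire |
|---|---|---|
| Planned 3:1 | 47% | 44% |
| 1:1, same total children | 54% | 49% |
| 1:1 sized to 80% main-effect power (12+12; 6+6 facilities) | 40% | 33% |

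Kani has only 8 EPI facilities, so 19 facilities cannot be split equally in Côte d'Ivoire; 11:8 gives 49%.

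**The case against.** Three objections have force.

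*The ratio may help.* If the total is allowed to follow from the ratio, as the section implies, 3:1 has more interaction power than a 1:1 design sized to the same main-effect power (47% versus 40%, 44% versus 33%). A reader might infer that 3:1 is simply the wrong direction for the distance question. The document does not support that without qualification: it holds only at a fixed total, and there the loss is modest. Low power comes mainly from testing an interaction.

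*The event rate may be too low.* The incidences used are reported under-5 figures. The active cohort tests every child at up to seven visits, Data analysis counts cases from either cohort, and it also combines the countries. The distance analysis is not confined to the active cohort. This stands, so no single power figure can be called the plan's own. It does not rescue a claim about any variation. At 1.5 per child-year the SE for a 10-point gradient is 0.152 × √(0.597/1.5) = 0.096 in Cameroon and 0.185 × √(0.572/1.5) = 0.114 in Côte d'Ivoire. Power is then Φ(0.143/0.096 − 1.96) = 32% and Φ(0.167/0.114 − 1.96) = 31%.

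*Some of this belongs in the analysis plan.* An exploratory label, or a rule for reading a non-significant result, may sit in the analysis plan, which is not shown. A reader might also infer that the investigators will take a null interaction as equal effectiveness; nothing in the protocol says so. The power claim, however, is made in the protocol itself.

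**Conclusion.** The point holds as an unsupported power claim. The sample size is a main-effect calculation, and on the documented incidences the active cohort in each country reaches about 80% power only for a near-far difference of roughly 30 percentage points. The percentages depend on an assumed control rate, equal tertiles, 20% loss, Poisson variation and single-country analysis. Across the gradients tried they run from about 15% to 97%, and higher rates, more data or pooling would raise them. No scenario examined gives sufficient power for any variation. The plan's facility numbers are not shown to be wrong, and the finding gives no reason to change them.

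**What to change.** In Sample size, remove the statement that 3:1 ensures sufficient power for any variation by distance. Replace it with the smallest area-by-distance interaction that the planned numbers can detect at 80% power, stating the assumed event rate, the gradient and the data source (active cohort alone or with passive cases; one country or both). Under the assumptions above this is a ratio of rate ratios of about 1.53 in Cameroon and 1.68 in Côte d'Ivoire; the investigators should substitute their own expected rate if they have a better one. In Data analysis, report the distance analysis as an area-by-distance interaction estimate with its 95% CI.

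Enrolment and allocation stay as they are. The cost is a change of wording and a less favourable stated capability for the distance question.

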## Methods

### Study site

Areas with the highest malaria transmission in both Cameroon and Côte d’Ivoire were purposively selected to be PMC implementation areas to maximize any observable impact of the intervention. Control areas in both countries were also identified that had epidemiological profiles that were similar to the intervention areas. In Cameroon, we chose Soa and Mbankomo in the Central Region as the intervention and the control areas, respectively, whilst in Côte d’Ivoire, Séguéla and Kani in the Worodougou Region were chosen as the intervention and control areas, respectively. These sites were chosen based on the size of the population, number of EPI facilities, malaria incidence, EPI coverage, and availability of a suitable control population receiving standard of care (Fig. 2).

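### The Cameroon sample size needs 26 intervention EPI facilities, but Soa, the only intervention area, has 20

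*Protocol article*

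**What the plan says.** All references are to the protocol article.

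- **Required number (Sample size).** The Cameroon calculation ends with "requiring 26 intervention and 9 control EPI facilities are required". With 20% loss to follow-up, this becomes 1,560 intervention and 540 control children over 18 months. The section describes its allocation as "accounting for a 3:1 sampling ratio of intervention to control to ensure sufficient power to assess any variation in PMC effectiveness" by distance to the EPI facility.
- **Which area is which arm (Study site).** "we chose Soa and Mbankomo in the Central Region as the intervention and the control areas, respectively". Each arm in Cameroon is one area.
- **Available number (Cameroon site description).** For Soa: "Of the 39 facilities, 20 administer EPI services and are eligible for SP administration as part of the expanded PMC programme". For Mbankomo: "Of the 32 facilities, 19 administer EPI services and are eligible for SP administration as part of the standard of care PMC programme".
- **Who can be selected (Study design and Table 1).** "All health facilities providing EPI services in selected study sites and corresponding catchment populations will be eligible for inclusion", with the facility inclusion criterion "Administer EPI/PMC services". Facilities without EPI services enter only for passive cohort data collection. On selection: "Health facilities will be randomly selected for inclusion".

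**The concern.** The required number of intervention clusters exceeds the number in the sampling frame. The number of facilities per arm drives the precision of a clustered comparison, and the Cameroon child targets and stated 80% power were built on it. If 26 cannot be reached, the sample size statement does not describe the study that will be done. A reader then cannot tell how many facilities and children Cameroon will have, what the allocation ratio is, whether Soa facilities are a random sample or a complete set, or what power applies.

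**Working it through.** **1. Count against the frame**

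| Area | Required | Eligible EPI facilities | Feasible |
|---|---|---|---|
| Soa (intervention) | 26 | 20 | No, short by 6 |
| Mbankomo (control) | 9 | 19 | Yes |
| Séguéla (intervention) | 14 | 41 | Yes |
| Kani (control) | 5 | 8 | Yes |

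The shortfall is 6/26 = 23%. The Cameroon total of 26 + 9 = 35 is below 20 + 19 = 39, but each arm is tied to one area, so spare Mbankomo facilities cannot serve as intervention clusters.

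**2. Is 26 a misprint?**

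1,560/26 = 60 and 540/9 = 60 children per facility, so the child targets rest on 26 and 9.

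The figures can also be reproduced with the Hayes-Bennett formula for rates with unequal arms:

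c0 = (1.960 + 0.842)² × [v0 + v1/r] / (λ0 − λ1)², where v = λ/y + k²λ².

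Inputs:
- λ0 = 0.597 per child-year. This is the 2020 under-5 incidence in the site description; the Sample size section gives no planning rate, so it is an assumption.
- λ1 = 0.70 × 0.597 = 0.4179 (the stated 30% reduction).
- y = 60 × 0.8 × 1.5 = 72 child-years per facility.
- r = 26/9 = 2.89.
- k = 0.25, read as the between-facility coefficient of variation (CV). The article calls 0.25 an intra-cluster correlation coefficient (ICC).
- Two-sided 5% test (sidedness is not stated).

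Results:
- v0 = 0.597/72 + 0.0625 × 0.597² = 0.03057
- v1 = 0.4179/72 + 0.0625 × 0.4179² = 0.01672
- c0 = 7.849 × (0.03057 + 0.01672/2.889) / 0.1791² = 8.90
- c1 = 8.90 × 2.889 = 25.70

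These round up to 9 and 26, so 26 looks like a calculated figure that was not checked against the number of eligible facilities. With 0.25 taken literally as an ICC (design effect on two proportions), about 22 and 62 to 63 facilities are needed, which does not reproduce the plan.

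**3. Illustrative power for layouts that exist**

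Power = Φ[(λ0 − λ1)/√(v0/m0 + v1/m1) − 1.960], with m1 intervention and m0 control facilities.

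| Layout | Children at 60 per facility | Ratio | CV 0.20 | CV 0.25 | CV 0.40 |
|---|---|---|---|---|---|
| 26:9 (as written) | 1,560 + 540 | 2.9 | 90.5% | 80.5% | 49.1% |
| 20:9 | 1,200 + 540 | 2.2 | 89.1% | 78.6% | 47.4% |
| 20:10 | 1,200 + 600 | 2.0 | 91.5% | 81.9% | 50.6% |
| 20:15 | 1,200 + 900 | 1.3 | 97.2% | 91.6% | 63.5% |

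Keeping 1,560 children in 20 facilities means 1,560/20 = 78 per facility. With 78 in both arms (62.4 retained, 93.6 child-years), 20:9 gives 81.3%. If 0.25 really is an ICC, power is 44.8% at 26:9 and 42.2% at 20:9. Under every reading, the step from 26:9 to 20:9 costs fewer than 3 percentage points.

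**The case against.** **Fig. 3 may settle the number.** It reports facility sample sizes and exclusions and is not available here. It may show how many facilities were actually selected. That is fair, but no selected number makes 26 fit into 20. If the figure shows another number, the Sample size text still needs correcting.

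**The effect on power is small.** This stands. Keeping the 9 controls costs about 2 points at CV 0.25, and one more Mbankomo facility restores 80%. A reader might infer that the Cameroon comparison is unworkable or badly underpowered because of the shortfall; the figures do not support that. Nor would the plan force the control arm down to 7 facilities just to hold the ratio.

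**The power figures are conditional.** This also stands. They depend on reading 0.25 as a CV and on an assumed control rate. The shortfall of 6 depends on neither.

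**The 3:1 rationale.** A reader might go further and call the stated reason for 3:1 mistaken, since variation in effectiveness by distance needs control children too. That is not shown. The factor 1/m1 + 1/m0 (0.150 at 26:9, 0.117 at 20:15) concerns the overall contrast between arms. Distance is measured per child and varies within catchments, and no variance for an arm-by-distance interaction has been computed. A large intervention arm also helps describe outcomes by distance and dose within that area.

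**Côte d'Ivoire.** A reader might extend the point there. Its counts are feasible, so there is no defect to correct.

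**Conclusion.** The point holds as an internal contradiction between the Cameroon site description and the Sample size section. Six of 26 required intervention clusters do not exist under the article's own eligibility rules. The 26:9 layout cannot be run as written, and the plan's near-3:1 ratio would become 2.2:1 at 20:9. If all 20 Soa facilities are used, no random selection remains there. This conclusion rests only on printed counts.

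The formula behind 26 and 9 can be reproduced, so the fault is in the match to the sampling frame and not in the arithmetic. Under the stated assumptions, the power lost is about 2 points (80.5% to 78.6%) and can be recovered with facilities that exist. The absolute level is uncertain: across a CV of 0.20 to 0.40 it runs from 89% to 47% at 20:9. Correction is needed because the primary sample size of one of two countries states a number that cannot be achieved. It does not mean that the study cannot answer its question.

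**What to change.** Reconcile the two sections and restate for Cameroon:

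1. facilities per arm, with at most 20 in Soa and 19 in Mbankomo;
2. children per facility and per arm;
3. the resulting allocation ratio;
4. the power for that layout, with the control rate stated and 0.25 identified as a CV or an ICC;
5. if all Soa EPI facilities are included, a plain statement of this in Study design, with random selection limited to the areas where it happens.

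Several layouts would serve. 20:10 restores about 80% power under the assumptions above with 1,800 children. Moving the six missing facilities to the control area (20:15) keeps 35 facilities and 2,100 children and gives about 91.6%. The latter is only an option: it needs 15 × 60 = 900 Mbankomo children aged 6 to 9 months, and the article does not say how many are available. It also adds census work and three-monthly updates in six more catchments.

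The text change itself costs little. The field cost depends on the layout chosen. Côte d'Ivoire needs no change on this point.
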